### Ethics and dissemination

#### Research ethics approval

The study protocol, involving recruitment, consent and data collection tools was reviewed and approved by the Institutional Review Board of the Second Affiliated Hospital of Xinxiang Medical University Committee (Approval Code: XYEFYLL-2024-82). All individuals will sign an informed consent before they are enrolled in the study.

#### Protocol amendments

Any substantial modifications to the protocol will be submitted to the Research Ethics Committee of the Second Affiliated Hospital of Xinxiang Medical University. Upon approval, these protocol amendments will be formally communicated to the relevant parties and documented in the Chinese Clinical Trial Registry.

#### Confidentiality

All study staff are trained and certified in basic human subjects research protections by the Second Affiliated Hospital of Xinxiang Medical University Training Program to ensure confidentiality. Furthermore, the Principal Investigator provides continuous training and oversight to the evaluation coordinator to ensure the confidentiality and privacy of all participants and their data.

#### Data sharing

Raw data will be generated at the Second Affiliated Hospital of Xinxiang Medical University. Derived data supporting the findings of this study will be available from the corresponding author [name] upon request.

## Discussion

To the best of our knowledge, this represents the first randomized, double-blind, sham-controlled trial designed to assess the synergistic effects of tDCS and MT on cognitive impairments in patients with stable schizophrenia. Cognitive impairment constitutes a core symptom that substantially impacts the quality of life and social functioning of patients. In this context, we present an innovative study protocol to investigate the potential for cognitive improvement in schizophrenia through the combination of tDCS and MT. We hypothesize that the group receiving both active tDCS and MT will exhibit more pronounced effects compared to those receiving either tDCS or MT alone. If our hypothesis is validated, this study will offer an effective therapeutic strategy of cognitive impairments, thereby aiding clinical psychiatrists and potentially improving patients’ quality of life and social functioning. Considering the tDCS might be widely accessible for home use and the existing evidence supporting the efficacy of MT, this combination appears to be a promising approach for translational application in clinical practice. The implementation of this strategy could yield substantial clinical and economic benefits in the treatment of schizophrenia. This study will provide important references for future larger-scale clinical trials and is expected to promote the widespread application of combined tDCS and MT in clinical practice.

In this study, we intend to employ tDCS targeting the mPFC to ameliorate cognition deficits in schizophrenia. The mPFC plays a crucial role in the cognitive functions that are disrupted in schizophrenia, and its dysfunction is closely associated with cognitive impairments (42). Research by Pomarol-Clotet et al. identified the mPFC as a significant brain region of abnormality in schizophrenia using voxel-based morphometry, functional magnetic resonance imaging, and diffusion tensor imaging techniques (43). Correspondingly, enhancing mPFC activity through tDCS techniques has been suggested as a potential strategy for cognitive improvement in individuals with schizophrenia. Previous study found that active tDCS targeting the mPFC caused significant activation of the insula and decreased activation of the amygdala, which correlated with improvements in attention and working memory (16). Mechanistically, tDCS may facilitate these effects by inducing long-term potentiation (LTP)-like neuroplasticity changes (44). tDCS is posited to activate N-methyl-D-aspartic acid (NMDA) receptors in cortical neurons, and thereby modulating the release of neurotransmitters such as gamma-aminobutyric acid (GABA) and dopamine. This modulation potentially facilitates long-term potentiation (LTP) and long-term depression (LTD), enhances synaptic efficacy, and improves the efficiency of signal transmission within neural pathways (45–48). Furthermore, tDCS has been demonstrated to elevate the secretion of brain-derived neurotrophic factor (BDNF), a neurotrophin crucial for neuronal survival, neuroplasticity, and memory function (49). Collectively, tDCS targeting mPFC has emerged as a promising approach for cognitive enhancement in individuals with schizophrenia, potentially influencing the biological processes involved in LTP and neuroplasticity.

As an adjuvant treatment of schizophrenia, MT has demonstrated efficacy in enhancing cognitive function and psychological well-being, ameliorating psychotic symptoms, and improving quality of life (50, 51). From a clinical perspective, MT provides a safe and enjoyable therapeutic environment that facilitates increased patient engagement and treatment compliance. Research indicates that MT enhances arousal and emotional engagement, which can subsequently improve cognitive performance on memory-related tasks. Neuroimaging studies have demonstrated that MT activates brain regions associated with cognitive processing, potentially enhancing memory, attention, and executive functions (52). This effect has been observed in the mPFC, hippocampus, amygdala, insula, cingulate cortex, and hypothalamus (22). Notably, MT has been suggested to promote neuroplasticity in the brain, thereby facilitating the reorganization of sensory information storage and utilization (53). Mechanistically, the integration of somatosensory and auditory training can induce more pronounced plasticity changes in the auditory cortex compared to auditory training alone (54). This approach engages the brain’s emotional and cognitive regions, thereby enhancing neuroplasticity and strengthening neural connections. Functional neuroimaging studies provide evidence that MT can influence activity within limbic and paralimbic regions (55). Wang et al. demonstrated that a five-week MT alleviate overall symptoms, enhance social cognition in individuals with schizophrenia, and modulate neural oscillations, specifically decreasing theta oscillations in the parietal lobe and increasing gamma oscillations in the mPFC (56). Interestingly, mPFC mediates cognitive functions through its synaptic connections with these limbic and paralimbic brain regions (52). Collectively, these findings suggest that MT may enhance cognitive functions such as attention and working memory by modulating brain activity and neuroplasticity in the mPFC associated with cognitive processing.

The main innovation of this study is that the combination of tDCS targeting mPFC and MT may have synergistic effects to enhance cognitive improvement in patients with schizophrenia. tDCS targeting mPFC modulates t cortical excitability, thereby enhancing prefrontal activity and promoting neuroplasticity. MT can activate mPFC, which plays a crucial role in memory and attention processes, thereby potentially amplifying the effects of tDCS (57). The integration of tDCS and MT may present a novel therapeutic strategy designed to enhance cognitive rehabilitation efforts. Furthermore, this approach minimizes physical discomfort and potential side effects for patients and can be easily administered in a home setting, thereby increasing the convenience and accessibility of treatment. Additionally, the relatively low cost of tDCS and MT makes this treatment method more economically feasible compared to more complex neuromodulation techniques, such as transcranial magnetic stimulation. The integration of tDCS and MT is based on the observation that they share the similar mechanisms of action at the neural level, specifically through the modulation mPFC activity and neuroplasticity. The application of tDCS during music listening appears to enhance neural responses that are otherwise suppressed when tDCS is administered alone. Hence, if we can demonstrate combining tDCS with MT enhances cognitive improvement in schizophrenia, it might alleviate the disease burden and improve patient health outcomes.

As a non-pharmacological intervention, the combination of tDCS and MT can serve as a valuable adjunct to traditional antipsychotic medications. First, patients with schizophrenia often require long-term use of antipsychotic medications, which may lead to side effects such as extrapyramidal symptoms, endocrine disturbances, and metabolic issues. As non-pharmacological interventions, tDCS and MT may help mitigate these adverse effects, thereby improving patients’ overall quality of life. Second, the accessibility of tDCS and MT makes this combination a promising option for widespread clinical use. tDCS devices are relatively portable and easy to operate, and MT is simple to implement. If future research confirms the efficacy of this intervention, it could be widely adopted in various settings, including community health centers, rehabilitation facilities, and even home-based care. Third, the cost-effectiveness of tDCS and MT makes this combination a promising option for widespread clinical use. Future research should focus on identifying the optimal parameters for tDCS and MT, as well as developing standardized protocols for their use in clinical practice.

Regarding neuropsychological assessments, we will utilize fNIRS to monitor hemodynamic changes in the cerebral cortex to evaluate the synergistic effect. As a direct measure of neural activity, fNIRS can assess both local and network effects. Notably, fNIRS can be used to measure neural activity in specific brain regions, allowing for correlations with cognitive functions and the prediction of treatment response outcomes. The combined non-pharmacological treatment is expected to result in a more substantial alteration in prefrontal activity. We also expect that these changes will be associated with improvements in cognitive function. Consequently, the findings of this study will provide valuable insights into the potential mechanisms underlying combined treatment. Additionally, we will explore the mechanistic factors contributing to the significant differences observed among five groups. Blood and Zetore utilized positron emission computed tomography (PET) to detect alterations in cerebral activity through changes in regional cerebral blood flow (rCBF) during MT, they found that MT increased rCBF in the ventral striatum, orbitofrontal cortex, insula, and ACC, and decreased rCBF in the mPFC, hippocampus, and amygdala (58). Prior studies utilizing fNIRS have demonstrated that MT may assist individuals with memory impairments in improving episodic memory by reducing prefrontal activity (59). Taken together, this neurophysiological approach offers mechanistic evidence supporting the effectiveness of tDCS combined with MT, highlighting its potential as a non-pharmaceutical treatment for patients with schizophrenia in the long run.

Despite its advantages, this study has several limitations. Firstly, the relatively small sample size within each group may reduce the statistical power and limit the generalizability of the results. Secondly, this research will be conducted at a single site, which affects the external validity of the findings. Thirdly, the long-term effects and sustainability of the experimental treatment have not been comprehensively evaluated. Although the treatment period lasts for up to 4 weeks, the assessment of the long-term therapeutic effects after the treatment ends has not been conducted, which takes into account the limitation of the length of hospital stay. Therefore, the combined strategy warrants validation through larger, prospective multicenter studies to further investigate its long-term therapeutic effects on cognitive impairments in schizophrenia.

This randomized, double-blind, sham-controlled clinical study aims to demonstrate the synergistic effect of tDCS and MT on cognitive impairments, psychotic symptoms, and overall functioning in individuals with schizophrenia. Findings from this study may elucidate the potential mechanisms underlying the combined treatment on cognitive impairments and identify a novel target for schizophrenia. Given that the majority of schizophrenia patients experience a significant burden from pharmacological treatments, the implementation of non-pharmaceutical treatments holds considerable importance for both patients and clinical psychiatrists.

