## Abstract

**Background:**

Despite numerous pharmacological treatments, individuals with schizophrenia continue to exhibit significant residual cognitive impairments, adversely affecting the progression of the illness and their overall quality of life. Preliminary evidence indicates that transcranial direct current stimulation (tDCS) and music therapy (MT) may offer potential benefits for enhancing cognitive function in schizophrenia. This study aims to examine the synergistic efficacy of tDCS and MT on cognitive impairments in individuals with schizophrenia and to elucidate the potential mechanisms involved in this process.

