This study protocol proposes a non-pharmacological approach by integrating tDCS with MT to investigate their synergistic effects on cognitive impairments in individuals with schizophrenia.This proof-of-concept study has three overall objectives. The first objective is to assess the efficacy of tDCS combined with MT on the treatment of cognitive impairments in patients with schizophrenia. We hypothesize that the integration of tDCS with MT will demonstrate greater effectiveness in ameliorating cognitive impairments compared to the application of either MT or tDCS. The second objective is to evaluate the efficacy of this integrated treatment approach on the positive and negative symptoms, as well as the quality of life, and social functioning. We expect that tDCS combined with MT will ameliorate both positive and negative symptoms and enhance overall functioning. The third objective is to investigate hemodynamic changes in the brain and explore the neural mechanisms involved in this combined treatment process by utilizing fNIRS during verbal fluency tasks (VFT). We propose the hypothesis that combined treatment will ameliorate prefrontal dysfunction, as measured by fNIRS, with more pronounced improvements observed in the combined group compared to those receiving tDCS or MT alone.

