### Statistical methods

The Shapiro-Wilk Test will be used to analyze whether the data conform to normality. If the quantitative data conform to a normal distribution, they will be expressed as the mean and standard deviation (SD); if they do not, they will be displayed as median values and interquartile range (IQR). Categorical data will be presented as counts with percentages. To evaluate differences in baseline characteristics between groups, t-tests, nonparametric tests, chi-square tests, Mann-Whitney U tests, and ANOVA will be employed appropriately. The Fisher exact test or χ² test will be used to compare adverse effects between groups.

In accordance with the CONSORT guidelines, analyses will be conducted following the intention-to-treat (ITT) principle, whereby all participants will be analyzed as originally randomized. A line graph will be utilized to depict values across different time points. To evaluate between-group and within-group differences over time for both primary and secondary outcomes, we will appropriately apply generalized linear mixed models and repeated measures ANOVA. A stepwise model selection process will be utilized to identify a parsimonious multivariable regression model. Age, gender and DDD doses of antipsychotic medications will be included as covariates in all models. The likelihood ratio test (LRT) will be utilized to assess the treatment effect by determining whether the coefficients for both the treatment and the interaction between time and treatment in the model are equal to zero. To account for multiple comparisons across multiple time points, p-values will be adjusted using the Bonferroni correction method. All statistical analyses will be conducted using SPSS 20.0. P < 0.05 is considered to be a statistically significant difference.

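### Synergy is the declared aim, but the stated hypotheses and test cannot tell synergy from additivity, so two merely additive treatments could be reported as synergistic

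*Protocol article*

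**What the plan says.** **Aim.** The Abstract states "This study aims to examine the synergistic efficacy of tDCS and MT on cognitive impairments in individuals with schizophrenia". The objectives paragraph of the Background and the opening of the Discussion also describe the study as one of synergistic effects. The closing paragraph of the Discussion goes further: the trial "aims to demonstrate the synergistic effect of tDCS and MT on cognitive impairments, psychotic symptoms, and overall functioning in individuals with schizophrenia".

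**Hypotheses.** The Background expects that "the integration of tDCS with MT will demonstrate greater effectiveness in ameliorating cognitive impairments compared to the application of either MT or tDCS". The Discussion repeats that "the group receiving both active tDCS and MT will exhibit more pronounced effects compared to those receiving either tDCS or MT alone". Both are statements of superiority over each single treatment.

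**Analysis.** For between-group and within-group differences over time, Statistical methods says "we will appropriately apply generalized linear mixed models and repeated measures ANOVA". The treatment effect is assessed with a likelihood ratio test, "determining whether the coefficients for both the treatment and the interaction between time and treatment in the model are equal to zero". On multiplicity it says "To account for multiple comparisons across multiple time points, p-values will be adjusted using the Bonferroni correction method". The only interaction named is time by treatment. The article names no tDCS-by-MT term, factorial coding or difference of differences.

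**Design.** Study design gives five equal arms: active tDCS plus MT (Group 1), sham tDCS plus MT (Group 2), active tDCS (Group 3), MT (Group 4) and control (Group 5). Under Music therapy, Group 5 continues its usual medication and receives neither intervention.

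**The concern.** In the usual statistical sense, synergy means that the combination does more than the sum of its parts. That is a claim about a tDCS-by-MT interaction. Showing that the combination beats each part does not establish it, because two treatments that work independently and add up also pass that test. A joint test over five arms says even less, since a difference between any of the arms can make it significant.

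At stake is the trial's headline conclusion. The aim speaks of synergy, the hypothesis of superiority, and nothing in the stated analysis links the two. An author or reader could take success on the second as evidence for the first. The four cells needed to estimate the interaction are already in the design, but the stated analysis does not use them for this.

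**Working it through.** **1. What the trial is sized for.** Sample size calculation gives alpha 0.05, power 80%, effect size 0.25 (read as Cohen's f), a repeated measures ANOVA and 45 participants. Assume the group-by-time test with k = 5 groups, m = 3 visits, within-person correlation 0.5 and no sphericity correction; the article states neither of the last two.
- Noncentrality = f² × N × m / (1 - 0.5) = 0.0625 × 45 × 3 / 0.5 = 16.875.
- Degrees of freedom: (5 - 1)(3 - 1) = 8 and (45 - 5)(3 - 1) = 80.
- Power = 0.810, so 45 is reproduced.
- Dropout: 45 / (1 - 0.2) = 56.25, rounded up to 57 and then to 12 per arm, which gives 60.

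The sizing therefore fits an 8-df group-by-time test, not a synergy contrast.

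**2. The stated test.** With a five-level group factor and three visits, the joint test of treatment and time by treatment has 4 + 8 = 12 degrees of freedom. It rejects for any pattern of arm differences.

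**3. Pure additivity.** Let each component add d to the change score. The means are then 0 in Group 5, d in Groups 3 and 4, and 2d in Group 1.
- Group 1 - Group 3 = d and Group 1 - Group 4 = d, so superiority over both is true.
- (Group 1 - Group 4) - (Group 3 - Group 5) = d - d = 0, so there is no synergy.

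**4. How often superiority succeeds with zero synergy.** Simulation with 12 per arm, pooled five-arm error (55 df) and unadjusted two-sided 0.05. The change-score SD is set to 1. Adjusting for baseline at correlation 0.5 gives a residual SD of √(1 - 0.25) = 0.866.

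| d per component | Group 1 beats both 3 and 4: change score | Same, baseline-adjusted | Five-arm F test at one visit (change score) | Synergy contrast rejects |
|---|---|---|---|---|
| 0.5 SD | about 10% | about 15% | 43% | about 5% |
| 0.8 SD | 32% | 45% | 87% | about 5% |
| 0.97 SD | 49% | 65% | 97% | about 5% |

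The synergy contrast keeps its nominal 5% error rate throughout.

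**5. What the synergy contrast can deliver at 12 per arm.**
- Standard error = √(4/12) × SD = 0.577 SD, against √(2/12) × SD = 0.408 SD for a pairwise comparison.
- Half-width of the 95% interval = 2.004 × 0.577 = 1.16 SD, or 1.16 × 0.866 = 1.00 SD with baseline adjustment.
- Power is 14%, 28% and 40% for a synergy of 0.5, 0.8 and 1.0 SD (change score).
- 80% power needs 1.65 SD, or 1.65 × 0.866 = 1.43 SD with baseline adjustment.

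**6. Why Group 4 and not Group 2.** Let t, m and s be the tDCS, MT and synergy effects and p an additive placebo response to the device. The means are t + m + p + s (Group 1), m + p (Group 2), t + p (Group 3), m (Group 4) and 0 (Group 5).
- With Group 4: (t + p + s) - (t + p) = s.
- With Group 2: (t + s) - (t + p) = s - p.

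There is no arm with sham tDCS alone, so the Group 2 version leaves the device response uncancelled.

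**The case against.** The strongest reply is that the article never says it will call superiority synergy. A reader might infer that additive results **would** be published as synergistic. The documents do not support that: the Discussion says only that, if the hypothesis is confirmed, the study will offer an effective therapeutic strategy, which is an efficacy claim. What stands is that they could be, because the aim speaks of synergy and nothing stated separates the two.

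Second, the article does not define synergy and uses the word loosely; the Background even credits MT alone with synergistic effects. The defect is partly one of wording, which is why rewording the aim is part of the remedy.

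Third, large assumed effects flatter the figures. The Background cites a medium effect of prefrontal tDCS on working memory, and at 0.5 SD per component the combination beats both single arms in only about 10-15% of trials. The simulation is also unadjusted, whereas the article plans a Bonferroni correction across time points, which would lower the percentages. Both points are fair, and they limit how often the problem would arise.

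Fourth, a five-arm mixed model already contains the contrast, and listing contrasts can be left to an analysis plan that is not shown. That would excuse silence. Here, however, the article itself states the aim, the hypotheses and the treatment-effect test, and these do not match.

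Finally, a reader might infer that adding the contrast settles the synergy question. It does not: at 12 per arm it mainly yields an estimate, and it is not sham-controlled.

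**Conclusion.** The concern holds in this form: the stated aim is synergy, the stated hypotheses and test concern superiority and any difference among arms, and additive treatments could therefore be reported as synergistic. That rests on the article's own text and on the algebra of additivity, and needs no numerical assumption.

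The size does need assumptions: equal component effects, normal errors, full retention at 12 per arm, unadjusted p-values, correlation 0.5 for the baseline-adjusted figures, and effects in SD units that the article does not supply. Under these, the probability of beating both single arms with no synergy runs from about 10-15% (0.5 SD per component) through 32-45% (0.8 SD) to 49-65% (0.97 SD).

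The mismatch does not bias the comparisons of the combination with each single treatment. It concerns what may be concluded from them.

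**What to change.** **Add to Statistical methods:** the contrast (Group 1 - Group 4) - (Group 3 - Group 5) on the T0-to-T2 change in the MCCB, taken from the primary mixed model and reported with its 95% confidence interval.

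**Limit the claim.** Use the word synergy only if the whole interval lies above 0, in the direction of benefit. An interval that merely excludes 0 is not enough, because a wholly negative one would indicate antagonism. Otherwise restrict the conclusion to the combination versus its components. Reword the aim in the Abstract, Background and Discussion to match.

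**State the limits of the contrast.** It compares an active device with no device, it is not sham-controlled, and it removes a placebo response to the device only if that response is additive with MT.

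**Other outcomes.** For psychotic symptoms and functioning, either report the same contrast descriptively or drop the synergy wording.

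**Timing and cost.** The rule should be fixed in writing before the first unblinding. It needs a few sentences and one extra contrast, with no additional patients, visits or assessments. The real cost is that the estimate will be imprecise, with 80% power only for about 1.4-1.65 SD at 12 per arm, so the synergy claim will probably have to be softened.
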